#### Acupuncture group

Participants in the acupuncture group will be treated by licensed acupuncturists with at least five years of clinical experience. All practitioners will undergo dedicated training on the study protocol and operating procedures before the start of the trial.

Acupoints: bilateral HT7 (Shenmen), PC6 (Neiguan) and SP6 (Sanyinjiao). Acupoint locations will follow the WHO Standard (24) Acupuncture Point Locations in the Western Pacific Region. Sterile, single-use stainless-steel needles (0.25 mm × 25 mm) will be used. After skin disinfection, needles will be inserted perpendicularly at each acupoint (HT7: 0.5–1 cun; PC6: 1–1.5 cun; SP6: 1–1.5 cun). Manual stimulation (twirling, lifting and thrusting) will be applied to elicit the deqi sensation. Needles will be retained for 30 minutes, with additional mild stimulation every 10–15 minutes if needed.

### Treatment fidelity and adherence

To promote intervention fidelity, all practitioners and staff will receive standardized training before the trial. To improve positioning reproducibility across sessions, bilateral HT7, PC6, and SP6 will be re-identified at each treatment session using standardized anatomical landmarks by the same trained research personnel whenever possible. The irradiation outlets will be aligned with the marked acupoint sites before activation, and direct skin contact will be maintained throughout the session. Adjustable elastic straps and adhesive single-point irradiation modules will be used to minimize displacement and variability in positioning. The position and contact condition of each module will be checked at the beginning of treatment and, when necessary, during the session to maintain consistent alignment and skin-contact conditions across sessions. Checklists will be used during sessions to record adherence to operating procedures. Attendance at each treatment session will be recorded. Participant adherence will be monitored using attendance logs and brief compliance interviews, and reasons for missed sessions will be documented.

### Outcomes

#### Primary outcome

The primary outcome is the change in Insomnia Severity Index (ISI) total score from baseline to the end of the two-week intervention (week 2). The ISI is a 7-item self-report scale that assesses the severity of nocturnal and daytime components of insomnia over the past two weeks, with total scores ranging from 0 to 28. Higher scores indicate more severe insomnia. The ISI has been validated in Chinese populations and demonstrates good reliability and sensitivity to change (20, 21).

#### Secondary outcomes

Pittsburgh Sleep Quality Index (PSQI) to assess subjective sleep quality over the past month; because the PSQI recall window is longer than the 2-week intervention period, the week-2 PSQI analysis will be interpreted cautiously as a supportive secondary endpoint (25);Fatigue Severity Scale (FSS) to evaluate the impact and severity of fatigue on daily functioning (26);Patient Health Questionnaire-9 (PHQ-9) to assess depressive symptoms;Generalized Anxiety Disorder-7 (GAD-7) to assess anxiety symptoms;Heart rate variability (HRV) parameters, including SDNN, RMSSD, LF, HF, and LF/HF ratio, will be measured using the SA-3000P Mental Stress Analysis System (Medicore, Republic of Korea) under standardized short-term resting conditions with a finger-clip photoplethysmography (PPG) sensor to assess changes in autonomic regulation before and after the intervention. HRV is included as an exploratory physiological outcome and will be interpreted as reflecting autonomic regulation rather than sleep architecture directly (27–30).

#### HRV measurement procedure

HRV assessments will be performed using the SA-3000P Mental Stress Analysis System (Medicore, Republic of Korea), an HRV analysis platform equipped with both electrocardiography (ECG) and photoplethysmography (PPG) acquisition modalities. In the present study, short-term resting HRV will be obtained using the dedicated finger-clip PPG sensor supplied with the system. The device derives inter-beat interval (IBI) series from peripheral pulse-wave signals and provides time-domain and frequency-domain HRV indices, including SDNN, RMSSD, LF, HF, and LF/HF ratio. The HRV measurement device and sensor setup used in this study are shown in **Figure 3**.

**Figure 3 f3:**
[figure not shown]
SA-3000P system and sensor setup used for short-term resting HRV assessment. Heart rate variability (HRV) in this study is assessed using the SA-3000P Mental Stress Analysis System (Medicore, Republic of Korea) with a finger-clip photoplethysmography (PPG) sensor. The device is used for standardized 5-minute resting recordings under controlled conditions to obtain time-domain and frequency-domain HRV indices, including SDNN, RMSSD, LF, HF, and LF/HF ratio. HRV, heart rate variability; PPG, photoplethysmography; SDNN, standard deviation of normal-to-normal intervals; RMSSD, root mean square of successive differences; LF, low frequency; HF, high frequency.

Assessments will be conducted in a dedicated quiet room with the ambient temperature maintained at 23–25°C. After entering the room, participants will sit comfortably with both hands naturally relaxed on the thighs or desk and rest quietly for 5–10 minutes before data acquisition in order to reduce the influence of recent movement and transient emotional fluctuations on autonomic activity. Participants will be instructed to breathe naturally and steadily, to avoid intentional deep breathing or breath holding, and to refrain from talking or unnecessary body or finger movements during the recording period.

For signal acquisition, the finger-clip PPG sensor will be placed on the participant’s left index finger. Before measurement, the fingertip will be checked to ensure that the skin is clean and dry and that there is no obvious contamination, nail polish, or excessive nail length that might interfere with optical signal acquisition. Before formal recording, waveform preview and signal-quality checking will be performed. If the waveform is weak, irregular, or obviously affected by interference, the clip position will be adjusted and the connection rechecked until a clear and stable waveform is obtained. Once the signal is stable and artifact interference is minimal, 5 minutes of continuous resting data will be recorded for HRV analysis.

To improve data reliability, several quality-control procedures will be applied. First, during the recording period, participants will remain relaxed and quiet and will avoid talking, coughing, exaggerated swallowing, or finger movement; if obvious waveform distortion occurs, the measurement will be paused and repeated. Second, participants will be instructed to avoid alcohol intake and sleep deprivation within 24 hours before testing and to avoid strong tea, coffee, and vigorous exercise within 2 hours before testing. Third, participants with obvious arrhythmias that materially impair HRV interpretation, such as atrial fibrillation or frequent premature beats, will be excluded from HRV statistical analyses. Finally, all HRV measurements will be performed by the same trained researcher using the same device and under as consistent conditions as possible, including room environment, body position, pre-test rest period, recording duration, and approximate time of day.

Because the PPG-based approach provides pulse-to-pulse intervals as a surrogate for cardiac beat-to-beat intervals, HRV in this study will be interpreted as an exploratory physiological indicator of autonomic regulation rather than a direct measure of sleep architecture or sleep continuity. Accordingly, HRV findings will be interpreted with appropriate caution in light of measurement timing, peripheral perfusion conditions, and inter-individual heterogeneity.

#### Safety outcomes

Adverse events related to LLLT or acupuncture, such as skin irritation, transient dizziness, bleeding, hematoma or pain, will be monitored at each visit and recorded in standardized forms. Severity, duration and causal relationship with the intervention will be assessed and documented.

### Participant timeline

Study procedures will take place at baseline (week 0), during the treatment phase, at the end of treatment (week 2), and at follow-up (week 6). Baseline assessments include demographic data, medical history, physical examination, ISI, PSQI, FSS, PHQ-9, GAD-7, and HRV. At week 2, ISI, PSQI, FSS, PHQ-9, GAD-7, and HRV will be reassessed, and a brief physical examination or safety check will also be repeated to support adverse-event monitoring. At week 6, only ISI will be reassessed to evaluate the persistence of the primary insomnia-severity outcome. Sleep diaries, adverse events, and concomitant medications will be monitored throughout the study as specified in **Table 3**.

### Sample size calculation

The sample size was formally powered based on the primary outcome, which is the detection of a clinically and statistically significant difference in ISI scores between the two groups. In our single-arm pilot study of wearable LLLT involving 33 participants, the baseline ISI score was 15.12 ± 3.72 and the post-intervention ISI score after the 2-week intervention was 10.91 ± 4.44, corresponding to a mean reduction of 4.21 points. For the manual acupuncture comparator, a randomized controlled trial reported a mean ISI score of 13.4 ± 3.9 in the acupuncture group at 2 weeks post-treatment (baseline 17.1 ± 4.1)5. Because directly comparable head-to-head change-score data for wearable LLLT versus manual acupuncture were unavailable, the sample size calculation was based on post-treatment ISI means from our pilot LLLT data and a published acupuncture trial. This approach was used as a pragmatic estimate for the expected between-group difference at the primary endpoint, while the primary analysis will adjust for baseline ISI using ANCOVA. To establish superiority, we assumed a conservative between-group difference of 2.5 points in favor of the LLLT group. Using a two-sample t-test allowing unequal variances in PASS software (version 21.0.3), with a two-sided significance level of 0.05 and 80% power, the required sample size was calculated to be 90 participants, with 45 participants per group. Allowing for an anticipated 15% dropout rate to maintain statistical power, the final target sample size was set at 106 participants, with 53 participants per group.

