### Statistical analysis

All analyses will be performed using SPSS (version 26.0) or equivalent software. Two-tailed p-values < 0.05 will be considered statistically significant. The primary analysis will strictly follow the intention-to-treat (ITT) principle. For the primary superiority outcome, analysis of covariance (ANCOVA) will be employed. Although the primary endpoint is defined as the change in ISI from baseline to week 2, ANCOVA will be performed with the week-2 ISI score serving as the dependent variable, the treatment allocation (LLLT vs. acupuncture) as the fixed factor, and the baseline ISI score as a covariate (31). This approach is statistically equivalent to comparing change scores while providing better precision. Furthermore, this adjustment for baseline ISI is specifically chosen to align with the stratified block randomization procedure, thereby maximizing statistical power and precision in estimating the treatment effect.

Between-group differences in adjusted mean changes and their 95% confidence intervals (CIs) will be reported. Statistical superiority of LLLT over manual acupuncture for the primary endpoint will be considered supported if the two-sided p-value for the between-group difference is less than 0.05 and the entire 95% CI of the difference excludes zero in favor of the LLLT group (32).

The longitudinal trajectory of ISI across post-randomization assessments will be analyzed as a supportive repeated-measures analysis using a linear mixed-effects model. The model will include treatment group, time, and the group × time interaction as fixed effects, baseline ISI as a covariate, and participant-specific random intercepts to account for within-subject correlations. This model will be used to evaluate whether the between-group difference in insomnia severity is maintained at week 6.

Secondary continuous outcomes assessed at week 2 only, including PSQI, FSS, PHQ-9, GAD-7, and HRV indices, will be analyzed using analysis of covariance, with the week-2 value as the dependent variable, treatment group as the fixed factor, and the corresponding baseline value as a covariate. When model assumptions are markedly violated, appropriate transformations or non-parametric methods will be considered. A per-protocol analysis including participants with adequate adherence, defined as attending at least four of six sessions and having no major protocol deviations, will be performed as a sensitivity analysis.

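### The 2.5-point ISI planning difference is the raw gap between two studies with unequal baselines, rounded up; it is not conservative, and the cited data imply a smaller, less well-powered difference

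*Protocol article*

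**What the plan says.** The Sample size calculation section of the protocol article draws on two separate sources. For LLLT it uses a single-arm pilot of 33 people, in which "the baseline ISI score was 15.12 ± 3.72 and the post-intervention ISI score after the 2-week intervention was 10.91 ± 4.44", a mean reduction given as 4.21. For acupuncture it uses one arm of a published trial that "reported a mean ISI score of 13.4 ± 3.9 in the acupuncture group at 2 weeks post-treatment (baseline 17.1 ± 4.1". It explains that no head-to-head change data existed, that post-treatment means were used as a pragmatic basis, and that the primary analysis will adjust for baseline. It then states: "we assumed a conservative between-group difference of 2.5 points in favor of the LLLT group". A Welch t-test "with a two-sided significance level of 0.05 and 80% power" gives 45 per group, raised to 53 for 15% dropout.

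The primary outcome is change in ISI to week 2. The Statistical analysis section specifies an ANCOVA of week-2 ISI on treatment with baseline ISI as covariate. Randomisation is stratified by baseline ISI (8-14 or 15-21).

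**The concern.** The two source populations did not start at the same ISI level, so part of the gap in their post-treatment means was there before anyone was treated. In this trial both arms are drawn from one randomised population, so that part will not reappear as a treatment effect. A planning difference that includes it is larger than the sources support, and calling it conservative tells the reader the opposite.

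This matters most for a non-significant result. The Discussion presents the data-based sample size as a strength and says a finding of no meaningful difference will help guide clinical decisions. A reader who trusts 80% power for a cautious effect would take a null result as fairly strong evidence against superiority. If power for the difference the sources imply is nearer one half, a null result would be unsurprising even if LLLT performed as the pilot suggests.

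**Working it through.** **Inputs, all from the Sample size calculation section.** LLLT: baseline 15.12 (SD 3.72), post 10.91 (SD 4.44). Acupuncture: baseline 17.1 (SD 4.1), post 13.4 (SD 3.9). Two-sided alpha 0.05, 80% power, 45 evaluable per arm, 53 randomised per arm. The baseline-to-week-2 correlation r is not given. I assume 0.3 to 0.7, the same in both studies.

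**1. The plan's own figure reproduces.** Welch test, difference 2.5, SDs 4.44 and 3.9: power is 79.2% at 44 per arm and 80.1% at 45. Dropout: 90/0.85 = 105.9, hence 106.

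**2. Where 2.5 comes from.**
- Post-treatment gap: 13.4 - 10.91 = 2.49
- Baseline gap: 17.1 - 15.12 = 1.98
- Mean reductions: 15.12 - 10.91 = 4.21 and 17.1 - 13.4 = 3.70; difference 0.51

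**3. Baseline-adjusted difference implied by the sources.** Adjusted difference = 2.49 - b x 1.98, where b is the within-group slope of post on baseline. Two choices of slope:
- acupuncture study: b = r x 3.9/4.1 = 0.951r
- average of both studies: b = r x (3.9/4.1 + 4.44/3.72)/2 = 1.072r

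The root-mean-square post SD is sqrt((4.44² + 3.9²)/2) = 4.18, and the residual SD is 4.18 x sqrt(1 - r²).

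**4. Power of the ANCOVA.** Noncentral t with 2n - 3 df and noncentrality = adjusted difference / (residual SD x sqrt(2/n)). Worked case, r = 0.5, acupuncture slope, n = 45: 2.49 - 0.476 x 1.98 = 1.55; standard error 3.62 x sqrt(2/45) = 0.763; noncentrality 2.03; power 52%.

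| r | Residual SD | Slope used | Part removed (share of 2.49) | Adjusted difference | Power, 45/arm | Power, 53/arm |
|---|---|---|---|---|---|---|
| 0.3 | 3.99 | acupuncture | 0.57 (23%) | 1.92 | 62% | 69% |
| 0.3 | 3.99 | average | 0.64 (26%) | 1.85 | 59% | 66% |
| 0.5 | 3.62 | acupuncture | 0.94 (38%) | 1.55 | 52% | 59% |
| 0.5 | 3.62 | average | 1.06 (43%) | 1.43 | 46% | 52% |
| 0.7 | 2.98 | acupuncture | 1.32 (53%) | 1.17 | 45% | 52% |
| 0.7 | 2.98 | average | 1.49 (60%) | 1.00 | 35% | 40% |

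The LLLT pilot's slope used alone would lower these figures further. A simulation with the acupuncture slope and baseline ISI truncated to 8-21 gave 60%, 51% and 45% at 45 per arm, so the entry range makes little difference.

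**5. Reference points at 45 per arm for r = 0.3, 0.5, 0.7.**
- Power if the true difference is 2.5: 84%, 90%, 98%.
- Difference detectable with 80% power: 2.38, 2.16, 1.78 points.
- Power if the true difference is 0.51: about 9% to 13% across the range.

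**The case against.** The strongest defence is that the protocol hides nothing. It prints both baselines, says comparable change data were lacking, calls the estimate pragmatic and announces the baseline adjustment. The sample-size arithmetic is right, and the result will be read through a 95% CI, which shows precision whatever the planning power was. The alternative power figures also depend on a correlation the document does not give. All of this stands, but none of it justifies the word conservative: the full observed gap was used and rounded up, and the change difference follows from numbers in the same paragraph.

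A reader might also infer more than the documents support:
- **That ANCOVA strips out the whole 1.98 points, so that 2.5 is mostly baseline imbalance.** It removes slope x 1.98, which is 23-60% of 2.49 for the assumed r. Only on the raw change scale is the share 80% (1.98/2.49).
- **That 80% power is false, or that sizing on an unadjusted t-test is a fault.** Given a true 2.5, 80% is correct, and the t-test is the cautious choice because ANCOVA would give more.
- **That 2.49 against 0.51 disproves the sentence "This approach is statistically equivalent to comparing change scores while providing better precision".** Those figures come from two unrelated studies with unequal baselines. The sentence concerns a randomised trial, where post-score, change-score and ANCOVA contrasts have the same expectation. The wording is loose, but these data cannot refute it.
- **That 0.51 is the effect to expect.** With a slope below 1, raw change favours the study with the higher baseline, here acupuncture, so 0.51 is a lower bound. The timing phrase for the acupuncture mean could also be read as two weeks of treatment or two weeks after it, so the two reductions may not be like for like.

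**Conclusion.** The point holds as a fault in the planning input, not in the calculation. The 2.5 points are an unadjusted cross-study gap with no allowance for a 1.98-point difference in starting severity, and the label conservative is wrong. Allowing for baseline, the cited data imply about 1.0 to 1.9 points, for which 45 per arm gives about 35-62% power and 53 per arm about 40-69%. These ranges rest on the assumed r of 0.3 to 0.7, on the two slope choices shown, and on the two studies being comparable apart from baseline ISI. Power at 45 per arm comes back to about 80% only at r = 0, where adjusting for baseline would gain nothing. The validity of the primary test and its type I error are unaffected. What changes is how much weight a null result can bear.

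**What to change.** Reword the sample-size paragraph; the sample size and the analysis stay as they are.

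1. Delete the word conservative.
2. State that the 2.49-point gap is unadjusted for a 1.98-point baseline gap between the two sources, and that their mean reductions differ by 0.51.
3. Keep 80% power only as conditional on a true difference of 2.5 points.
4. Add the difference detectable by ANCOVA with 80% power at 45 per arm: about 2.4 points at r = 0.3, 2.2 at r = 0.5 and 1.8 at r = 0.7, with r labelled as assumed.
5. Add that power for the baseline-adjusted difference implied by the planning data is roughly 35-62%. If the 9-13% power at 0.51 is quoted, mark it as a lower bound and say why.

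The cost is a few sentences and a less favourable power statement; no participants or data are added. Trial status reports that recruitment is complete and no comparative analysis has been done, so the correction can still be made before results are known.

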### Statistical analysis

All analyses will be performed using SPSS (version 26.0) or equivalent software. Two-tailed p-values < 0.05 will be considered statistically significant. The primary analysis will strictly follow the intention-to-treat (ITT) principle. For the primary superiority outcome, analysis of covariance (ANCOVA) will be employed. Although the primary endpoint is defined as the change in ISI from baseline to week 2, ANCOVA will be performed with the week-2 ISI score serving as the dependent variable, the treatment allocation (LLLT vs. acupuncture) as the fixed factor, and the baseline ISI score as a covariate (31). This approach is statistically equivalent to comparing change scores while providing better precision. Furthermore, this adjustment for baseline ISI is specifically chosen to align with the stratified block randomization procedure, thereby maximizing statistical power and precision in estimating the treatment effect.

Between-group differences in adjusted mean changes and their 95% confidence intervals (CIs) will be reported. Statistical superiority of LLLT over manual acupuncture for the primary endpoint will be considered supported if the two-sided p-value for the between-group difference is less than 0.05 and the entire 95% CI of the difference excludes zero in favor of the LLLT group (32).

The longitudinal trajectory of ISI across post-randomization assessments will be analyzed as a supportive repeated-measures analysis using a linear mixed-effects model. The model will include treatment group, time, and the group × time interaction as fixed effects, baseline ISI as a covariate, and participant-specific random intercepts to account for within-subject correlations. This model will be used to evaluate whether the between-group difference in insomnia severity is maintained at week 6.

Secondary continuous outcomes assessed at week 2 only, including PSQI, FSS, PHQ-9, GAD-7, and HRV indices, will be analyzed using analysis of covariance, with the week-2 value as the dependent variable, treatment group as the fixed factor, and the corresponding baseline value as a covariate. When model assumptions are markedly violated, appropriate transformations or non-parametric methods will be considered. A per-protocol analysis including participants with adequate adherence, defined as attending at least four of six sessions and having no major protocol deviations, will be performed as a sensitivity analysis.

For the primary ANCOVA analysis, missing week-2 ISI data will be handled using multiple imputation under the missing-at-random assumption. The imputation model will include baseline characteristics, treatment allocation, and available outcome data, and results from imputed datasets will be combined using Rubin’s rules (33). For the supportive longitudinal ISI analysis, the linear mixed-effects model will use all available ISI observations under the same missing-at-random assumption. For secondary outcomes assessed at week 2 only, missing data will be handled using multiple imputation if the extent of missingness is substantial, and complete-case or imputation-based sensitivity analyses will be conducted as appropriate.

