Physical examination/safety check	×		×				
Interventions							
LLLT group		3 sessions	3 sessions				
Manual acupuncture group		3 sessions	3 sessions				
Outcome assessments							
ISI	×		×				×
PSQI	×		×				
FSS	×		×				
PHQ-9	×		×				
GAD-7	×		×				
HRV	×		×				
Process and safety monitoring							
Sleep diary	×	×	×	×	×	×	×
Adverse event monitoring		×	×	×	×	×	×
Concomitant medication recording	×	×	×	×	×	×	×
Dropouts/withdrawals		×	×	×	×	×	×
Participant adherence		×	×				

× indicates that the item is performed or assessed at the corresponding time point. LLLT, low-level laser therapy; ISI, Insomnia Severity Index; PSQI, Pittsburgh Sleep Quality Index; FSS, Fatigue Severity Scale; PHQ-9, Patient Health Questionnaire-9; GAD-7, Generalized Anxiety Disorder-7; HRV, heart rate variability. Week 0 indicates baseline, week 2 marks the end of treatment, and week 6 represents follow-up. Both interventions are delivered three times per week for 2 weeks, with six sessions in total. ISI is assessed at baseline, week 2, and week 6; PSQI, FSS, PHQ-9, GAD-7, and HRV are assessed at baseline and week 2. Sleep diaries, adverse events, concomitant medications, dropouts/withdrawals, and adherence are monitored as indicated.

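### The supportive week-6 model gives ISI one pooled variance for weeks 2 and 6, so the week-6 interval is miscalibrated, in an unknown direction, if those variances differ

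*Protocol article*

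**What the plan says.** The Statistical analysis section states that the course of ISI after randomization "will be analyzed as a supportive repeated-measures analysis using a linear mixed-effects model". It lists the terms: "The model will include treatment group, time, and the group × time interaction as fixed effects", together with "baseline ISI as a covariate, and participant-specific random intercepts to account for within-subject correlations". No baseline × time term is listed, and no residual variance structure is named.

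The purpose is stated next: "This model will be used to evaluate whether the between-group difference in insomnia severity is maintained at week 6". It is the only analysis that the article names for week 6.

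The note to Table 3 fixes the visits: "ISI is assessed at baseline, week 2, and week 6". With baseline as a covariate, each participant therefore contributes at most two outcome values to this model. For missing data, "the linear mixed-effects model will use all available ISI observations under the same missing-at-random assumption".

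**The concern.** With two outcome visits, a random intercept plus one residual variance has two covariance parameters. They leave a non-negative correlation between the visits free, but force week 2 and week 6 to share one total variance. Week 2 is the end of treatment and week 6 is four weeks later, so there is no particular reason for the spread of ISI, after adjustment for baseline, to be the same at both.

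If it is not, the week-6 contrast borrows precision from week 2, or loses precision to it. Its standard error and 95% CI are then too small or too large. Because no other week-6 analysis is named, nothing else in the plan would show this. What is at stake is the calibration of the persistence result; the primary week-2 conclusion is not involved.

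**Working it through.** **The plan's own figure.** The only related figure is the sample size. The Sample size calculation section says "we assumed a conservative between-group difference of 2.5 points in favor of the LLLT group", with post-treatment SDs of 4.44 (LLLT pilot) and 3.9 (published acupuncture trial), "with a two-sided significance level of 0.05 and 80% power". A two-sample t-test with unequal variances has power 79.2% at 44 per group and 80.1% at 45, so 45 per group reproduces. Allowing for 15% dropout, 90 / 0.85 = 105.9, so 106. This figure is correct but concerns week 2 only.

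**Assumptions, not in the documents.** Residual SD after baseline adjustment: 4.0 at week 2. Correlation between the two visits: 0.6. Residual SD at week 6: varied through r = SD(week 6) / SD(week 2).

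**Closed form, complete data.** The pooled model estimates one variance near (SD2² + SD6²)/2, whereas the true week-6 variance is SD6². Hence

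model SE / true SE ≈ √((1 + r²)/2) / r, and type I error ≈ 2 × [1 − Φ(1.96 × ratio)].

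- r = 0.8: √0.82 / 0.8 = 1.132; type I error 2.7%
- r = 1.0: ratio 1; 5.0%
- r = 1.2: √1.22 / 1.2 = 0.920; 7.1%
- r = 1.5: √1.625 / 1.5 = 0.850; 9.6%

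In ISI points with 53 per group and r = 1.2, the pooled variance is (16 + 23.04)/2 = 19.52. The model SE is √19.52 × √(2/53) = 0.858, against a true SE of 4.8 × √(2/53) = 0.932.

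**Simulation.** 106 participants, no treatment effect, 4000 runs per setting, REML random-intercept model with one baseline slope. The Monte Carlo error of a 5% rate is √(0.05 × 0.95 / 4000) = 0.34 percentage points.

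| r | Mean model SE | Empirical SD | Type I error, complete data | Type I error, 15% missing at week 6 |
|---|---|---|---|---|
| 0.8 | 0.704 | 0.625 | 2.2% | 2.8% |
| 1.0 | 0.779 | 0.786 | 4.9% | 4.8% |
| 1.2 | 0.861 | 0.940 | 7.3% | 7.4% |
| 1.3 | 0.903 | 1.003 | 7.5% | 8.6% |
| 1.5 | 0.994 | 1.165 | 8.9% | 10.0% |

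The SE columns are for complete data. At r = 1.2 the SE is 8% too small (0.861 / 0.940 = 0.92), and at r = 1.5 it is 15% too small. At r = 0.8 it is 13% too large. A separate week-6 ANCOVA, which has its own variance and slope, stays at 4.7–5.9% in every setting.

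**Single baseline slope.** With equal variances but true slopes of 0.6 at week 2 and 0.3 at week 6, type I error of the week-6 contrast is 5.2% with complete data and 4.3% with 15% missing. The common slope has almost no effect on error.

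**Group × time term.** Its type I error is 4.8–5.5% with complete data and 4.3–6.2% with 15% missing. With complete data it rests on within-participant differences, whose variance the random-intercept model estimates correctly even when the visit variances differ.

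**What a non-significant interaction could show.** Suppose the planned 2.5-point difference halves to 1.25 by week 6, with SD 4.0 at both visits and correlation 0.6. The SD of the within-person difference is 4 × √(2 × 0.4) = 3.58. With 45 per group the SE is 3.58 × √(2/45) = 0.754, and power is Φ(1.25/0.754 − 1.96) = 38%. With 53 per group the SE is 0.695 and power is 44%. Losing half the effect would thus go undetected more often than not. Complete loss would usually be detected (91% and 95%).

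**The case against.** The strongest objection is that the text never says the residual variances are equal. A random intercept with visit-specific residual variances has three covariance parameters, and for ordinary positive correlations it is equivalent to the unstructured matrix. The wording would allow that, and an analysis plan that is not shown may specify it. This stands as far as it goes: equal residual variance is the ordinary reading of the stated model, not its literal text. It does not remove the point, because the article presents a random intercept as the whole account of the covariance.

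It also stands that the analysis is labelled supportive, and that the superiority rule applies only to the separate week-2 ANCOVA.

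A reader might go further in three ways that the documents do not support.

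- That the week-6 interval is too narrow. No week-6 SD and no correlation between weeks 2 and 6 is given. The SDs in the Sample size calculation section move both ways from baseline to post-treatment: 3.72 to 4.44 for LLLT and 4.1 to 3.9 for acupuncture. Residual variance could rise simply because the link to baseline weakens. For example, with total SD 4.2 at both visits (an assumption) and correlation with baseline falling from 0.60 to 0.35, the residual SD goes from 4.2 × √(1 − 0.36) = 3.36 to 4.2 × √(1 − 0.1225) = 3.93, a ratio of 1.17. That makes inflation plausible, not established.
- That the random intercept forces a single baseline slope. The single slope comes from the unlisted baseline × time term, and its effect on error is negligible.
- That the protocol will read a non-significant interaction as persistence. No such rule is stated. The article does not say which quantity from the model decides, and the same model also yields the week-6 difference.

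**Conclusion.** The point holds as a minor one. On its ordinary reading, the only stated week-6 analysis uses a pooled variance, so the week-6 contrast has the right error rate only if the residual variances at weeks 2 and 6 are about equal. For SD ratios from 0.8 to 1.5 the type I error runs from about 2% to about 9% with complete data, and to 10% with 15% missing at week 6. These figures rest on an assumed week-2 residual SD of 4.0, a correlation of 0.6 and the assumed ratios. The closed form, which needs only the ratio, gives much the same values. Whether the interval will be too narrow or too wide cannot be told from the article. The group × time test and the primary result are not in question.

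**What to change.** Fit the same two-visit model with an unstructured 2×2 residual covariance in place of the random intercept, and optionally add baseline ISI × time. This keeps the planned use of all observed ISI values under missing at random, and gives a valid week-6 standard error whichever way the variance moves. State that the adjusted week-6 group difference with its 95% CI is the persistence result, and that persistence will not be inferred from a non-significant group × time term alone.

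The cost is a change of model syntax and one sentence. There is one extra covariance parameter (three instead of two), plus one slope if the interaction with baseline is added, which is small for about 106 participants. The Trial status section says that no comparative outcome analysis has been done, so the change can still be recorded before the allocation is revealed to the statisticians.
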